### Sample size calculation

3.5

The sample size calculation formula is as follows: 

[figure not shown]

In the above formula, *N* is the number of samples in each group, *p*_0_ is the incidence of outcomes in the non-exposed group, *p*_1_ is the incidence of outcomes in the exposed group, *c* is the ratio of the number of non-exposed and exposed groups, *α* is an acceptable type I error, *β* is an acceptable type II error, and *Z*_α_ and Z_*β*_ can be determined by looking them up in the *Z* value table.

The 1-year survival rate is expected to be 22% in the non-exposed group and 45% in the exposed group. Assuming a non-exposed group and an exposed group sample ratio of 1:1, the required sample size is estimated by SAS 9.4 software ([name]) to be at least 134 cases in the 2 groups, based on a 2-sided alpha at a significance level of 0.05 and the test efficacy 1-beta of 80%. Meanwhile, considering a dropout rate of 15%, we concluded that a total of 148 patients would need to be recruited to ensure significant results.

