### Determination of grouping

3.7

Patients will be divided into a non-exposed group (Western medicine treatment group) and an exposed group (integrated traditional Chinese and Western medicine treatment group), according to whether they will receive TCM treatment or not. The classification of the cohort is based on the time of exposure after all clinical data are collected, not set at the time of enrollment.

1.Western medicine treatment group: times of chemotherapy ≥2 courses.2.Integrated traditional Chinese and Western medicine treatment group: TCM treatment ≥12 weeks, times of chemotherapy ≥2 courses, TCM and Western medicine treatment can be performed simultaneously or before and after.

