#### Overall survival (OS)

4.1.1

The primary outcome of this study is OS, which is from enrollment to patient death or the end of the study (October 31, 2021).

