## Discussion

5

TCM has been used in China for thousands of years. In recent years, it has been gradually accepted by Western countries.^[19]^ In the literature,^[20,21]^ it has been reported that TCM plays an important role in reducing the side effects of chemotherapy and improving the survival of patients. In addition, studies^[22]^ have reported that TCM combined with chemotherapy can improve survival rates and quality of life. This study aims to assess the survival and quality of life of patients with advanced pancreatic cancer, refine the core pathogenesis of TCM for pancreatic cancer and core prescriptions, and ultimately provide reliable data support for the formation and application of clinical solutions for the treatment of pancreatic cancer using integrated Chinese and Western medicine.

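### Groups are fixed at the end by minimum treatment received while overall survival runs from enrollment: survival is inflated to the extent that qualifying treatment follows enrollment, and 148 patients leave no margin for the exclusions

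*Protocol article*

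**What the plan says.** Three parts of the protocol article bear on this.

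- **Group membership (3.7, Determination of grouping).** Classification is "based on the time of exposure after all clinical data are collected, not set at the time of enrollment". The non-exposed rule reads "Western medicine treatment group: times of chemotherapy ≥2 courses". The integrated group must meet the same chemotherapy minimum and also have at least 12 weeks of TCM, given together with chemotherapy or before or after it. No group is defined for a patient with fewer than 2 courses. The section does not say whether courses or TCM given before enrollment count.
- **Time origin (4.1.1, Overall survival).** OS is the primary outcome, "which is from enrollment to patient death or the end of the study".
- **Sample size (3.5).** The plan states: "The 1-year survival rate is expected to be 22% in the non-exposed group and 45% in the exposed group". It requires at least 134 patients in the two groups and recruits 148, "considering a dropout rate of 15" per cent. It gives no separate allowance for patients who fail the minimum-exposure rules.

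Section 3.3 (Shedding criteria) asks for a last follow-up of withdrawn and lost patients so that they can contribute to efficacy and safety. Section 3.7 gives those who leave before a second course no group to contribute to.

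**The concern.** The membership rule looks forward from enrollment, while the survival clock starts at enrollment. If the second course comes after enrollment, everyone analysed had to be alive when it was given. That stretch of follow-up is death-free by construction, and patients who died in it are left out of both groups. Absolute OS is then overstated relative to the enrolled population and to the 22% planning rate, and the analysed patients no longer represent those enrolled.

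The chemotherapy minimum is common to both groups, so this part is mainly about absolute OS and representativeness. The TCM minimum is not common. An integrated-group patient must survive long enough to accumulate 12 weeks of TCM, and a Western-group patient has no matching requirement. This favours the integrated group in the primary comparison even if TCM does nothing.

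The exclusions also reduce the analysed number, and the sample size has no reserve for them.

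**Working it through.** **Inputs from the document.** 1-year survival 22% and 45%, 1:1 ratio, two-sided alpha 0.05, power 80%, 134 required, 15% dropout, 148 recruited (all 3.5); median survival on Western treatment 6 to 11 months (Introduction).

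**Assumptions.** Exponential survival; 4, 6 or 8 weeks from enrollment to qualify on chemotherapy (course length is not given); TCM starting at enrollment, so 12 weeks to qualify on TCM; 4.345 weeks per month.

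**1. The plan's own figure.** For two proportions with pooled variance, n per group = (1.960 + 0.842)² × 2 × 0.335 × 0.665 / 0.23² = 66.1, rounded up to 67, so 134 in total. The stated 134 reproduces.

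**2. The dropout step.** 134 / (1 − 0.15) = 157.6, so 158 would have to be recruited. 148 × 0.85 = 125.8, about 126, which is 8 short of 134. The stated 148 matches a 10% uplift (134 × 1.10 = 147.4), not 15%. By the Fleiss formula, power is 81.3% at 134 and 78.7% at 126. The largest total loss that still leaves 134 is 14 / 148 = 9.5%.

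**3. Guaranteed survival time.** Monthly hazards are −ln(0.22)/12 = 0.126 and −ln(0.45)/12 = 0.0665. Apparent 1-year survival among those alive at the qualifying time t is S(12 months) / S(t).

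| Weeks to qualify | S(t), 22% group | Apparent 1-year | S(t), 45% group | Apparent 1-year |
|---|---|---|---|---|
| 4 | 0.890 | 24.7% | 0.941 | 47.8% |
| 6 | 0.840 | 26.2% | 0.912 | 49.3% |
| 8 | 0.793 | 27.8% | 0.885 | 50.9% |
| 12 | 0.706 | 31.2% | 0.832 | 54.1% |

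The chemotherapy rule therefore adds about 3 to 6 points to Western 1-year survival.

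**4. The one-sided part.** Let true 1-year survival be 22% in both groups. The integrated group, conditioned on 12 weeks, shows 31.2%. The Western group, conditioned on 4 to 8 weeks, shows 24.7% to 27.8%. The spurious gap is 31.2 − 27.8 = 3.4 to 31.2 − 24.7 = 6.5 points.

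**5. Numbers left, applying the chemotherapy rule only.** With 74 per group, 74 × (0.890 + 0.941) = 135 remain at 4 weeks, 74 × (0.840 + 0.912) = 130 at 6 weeks, and 74 × (0.793 + 0.885) = 124 at 8 weeks. If a further 15% drop out with no overlap, 115, 110 or 106 remain, and about 173, 180 or 188 would need to be enrolled to keep 134.

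**6. Sensitivity to the survival assumption.** An exponential curve with 22% at one year has a median of ln 2 / 0.126 = 5.5 months, a little below the document's 6 to 11 months. With those medians, deaths by 6 to 8 weeks are about 8% to 19%, against 16% to 21% in the 22% group above. For a median of 6 months, 1-year survival of 25% would appear as 27.8% to 30.9% (4 to 8 weeks). The rise is again about 3 to 6 points.

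**The case against.** The strongest reply is that Section 3.7 never says the courses must follow enrollment. Section 3.9 does use that qualifier, but only to divide treatment from follow-up, and the eligibility table is not shown. If earlier courses count, the death-free interval shrinks or vanishes for those patients. This stands, and it makes the finding conditional. Grouping by treatment still to be received, settled only once data are complete, suggests that much of the qualifying treatment comes after enrollment, but that is an inference.

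A reader might go further in four ways that the document does not support.

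- *That 148 cannot yield 134.* It can, if total loss is at most 9.5%. At 4 weeks to qualify, early deaths alone leave 135.
- *That the chemotherapy rule causes the shortfall.* The stated 15% dropout produces it unaided. Many who stop early through withdrawal, poor compliance or adverse events are already shed cases under Section 3.3, so the two losses may overlap, and 106 to 115 is a no-overlap figure.
- *That progression before a second course disqualifies a patient.* Section 3.7 does not stop counting courses at progression.
- *That the 2-course rule itself biases the comparison because TCM helps patients reach course 2.* The Discussion reports that "TCM plays an important role in reducing the side effects of chemotherapy", but as background, and it says nothing about completing courses. Section 3.7 also lets chemotherapy precede TCM. Such a bias is possible; neither its direction nor its size can be derived.

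The reply does not reach the 12-week TCM minimum. It applies to one group only, and to the extent that TCM is given after enrollment it creates an advantage unrelated to effect.

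**Conclusion.** The point holds in conditional form. Membership is decided by later treatment while OS starts at enrollment, so OS is inflated to the extent that the qualifying treatment follows enrollment. The size, about 25% to 28% instead of 22% in the Western group, rests on exponential survival and an assumed 4 to 8 weeks to qualify. The 2-course rule chiefly affects absolute OS and representativeness. The bias in the comparison comes mainly from the 12-week TCM minimum, about 3 to 6.5 points at one year under no effect, assuming that TCM starts at enrollment.

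On sample size, what follows from the document's own figures is that 15% dropout leaves about 126, not 134. Deaths before qualifying lower this further, by an amount that cannot be fixed from the document and may partly overlap with dropout. The problem touches the primary outcome and the planned number, and it should be corrected.

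**What to change.** 1. Make the primary analysis set all enrolled patients who start chemotherapy, and enter TCM in the Cox model as a time-dependent exposure. Alternatively, use one common landmark (delayed entry) in both groups, no earlier than the time by which both the 2-course and the 12-week TCM minimums can be met, with groups set by treatment received up to then. Starting the clock at the end of course 2 would not be enough, because survival up to 12 weeks of TCM would remain guaranteed in one group.
2. Keep the minimum-exposure groups of Section 3.7 as a sensitivity analysis.
3. State whether courses before enrollment count.
4. Report how many enrolled patients the rule excludes, and their survival.
5. Restate the expected analysable number and power for 148 enrolled, using the 15% dropout and an explicit allowance for patients who do not qualify.

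The cost is mostly wording and a different Cox model; chemotherapy dates and TCM duration are already needed for the grouping. The all-enrolled set will include patients with little treatment, and the landmark version drops early deaths and answers a question about survivors to that point. Either way, the stated analysable number and power become less favourable.

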### Division of treatment period and follow-up period

3.9

If the times of chemotherapy after enrollment are ≤4 courses, the follow-up period will be entered after the end of chemotherapy; if the times of chemotherapy after enrollment are >4 courses, the follow-up period will be entered after the fourth chemotherapy.

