##### Progression-free survival (PFS)

4.1.2.1

PFS, which is from enrollment to disease progression.

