##### Tumor markers

4.1.2.2

Tumor markers, including CA199, CEA, and AFP, are closely related to the treatment of pancreatic cancer. They are used as one of the indicators to evaluate the effectiveness of treatment and are recorded at baseline and at each treatment visit and follow-up periods.

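### The integrated group accepts TCM given in any order and is fixed after all data are in, so a patient who progresses before any TCM can count as an integrated PFS event

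*Protocol article*

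**What the plan says.** Section 3.7 (Determination of grouping) defines the integrated group by "TCM treatment ≥12 weeks, times of chemotherapy ≥2 courses", and on timing adds that "TCM and Western medicine treatment can be performed simultaneously or before and after". The groups are "based on the time of exposure after all clinical data are collected, not set at the time of enrollment". The section sets no date, visit or event before which the TCM must begin or the 12 weeks must fall.

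The outcome clock starts earlier. The PFS section reads "PFS, which is from enrollment to disease progression", and OS (section 4.1.1) also starts at enrollment. Tumor markers "are recorded at baseline and at each treatment visit and follow-up periods". Section 3.9 separates treatment from follow-up by the number of chemotherapy courses alone, so TCM given after chemotherapy can fall entirely in the follow-up period. Section 4.3.4 compares survival between the cohorts by log-rank test and adds Cox regression for influencing factors. It does not describe TCM as changing over time.

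**The concern.** Under this rule, exposure that happens later decides the group for outcomes that happened earlier. For PFS the consequence is concrete: the event can come before the first dose of the treatment it is credited to. Such a patient's PFS describes Western treatment alone but sits in the integrated arm.

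The same retrospective grouping creates guaranteed survival time in OS, because a patient must live long enough to complete 12 weeks of TCM. PFS needs separate attention: a patient need not be progression-free to qualify, only alive, so the PFS bias depends on when and why TCM was started. If it is left as it is, a PFS difference between the groups could come wholly from the grouping rule.

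**Working it through.** **Step 1. One patient through the rule.** Enrollment at week 0; at least 2 courses of chemotherapy, no TCM; progression at week 10; TCM from week 10 to week 22. Section 3.7: at least 2 courses, 12 weeks of TCM, sequential order allowed, so the group is integrated. PFS definition: 10 weeks, all without TCM. The log-rank test counts this as an integrated event.

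**Step 2. How often progression could come first among sequential users.** The article states no PFS figure, so there is none to reproduce. Assume exponential PFS with median *m* of 3 to 6 months, and TCM first started at week 8 (1.84 months) or week 12 (2.76 months). The share progressing before TCM is 1 − 0.5^(t/m):

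- t = 1.84, m = 6: 19%
- t = 2.76, m = 6: 27%
- t = 1.84, m = 3: 35%
- t = 2.76, m = 3: 47%

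These are shares of patients who turn to TCM only after chemotherapy. The number of such patients is unknown, and only those who go on to complete 12 weeks enter the integrated group.

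**Step 3. Effect on the comparison when TCM does nothing.** Simulation assumptions, none from the article unless noted:

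- exponential progression and post-progression times, with medians of 3 and 3, 4 and 4, or 6 and 5 months (sums of 6, 8 and 11, loosely matching the 6 to 11 months of median survival in the Introduction)
- 60% of patients intended for TCM, with start uniform over 0 to 3, 6 or 12 months and unrelated to progression
- deaths before 1.5 months excluded, as a stand-in for the two-course minimum
- exposed = alive to complete 12 weeks of TCM, as in section 3.7

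Spurious PFS hazard ratio, with the share of the exposed group that began TCM after progression in brackets:

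| Median PFS | Start 0–3 mo | Start 0–6 mo | Start 0–12 mo |
|---|---|---|---|
| 3 mo | 0.69 (16%) | 0.61 (25%) | 0.54 (33%) |
| 4 mo | 0.76 (14%) | 0.68 (23%) | 0.58 (32%) |
| 6 mo | 0.84 (10%) | 0.76 (18%) | 0.64 (26%) |

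The spurious OS hazard ratio in the same runs was 0.44 to 0.82. If all TCM began at enrollment, the PFS hazard ratio was still 0.83 to 0.93. Part of the bias therefore comes from requiring 12 weeks to be completed, and an early start alone does not remove it.

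**Step 4. Direction.** The true ratio is 1 throughout, and step 3 favours TCM in every cell, but only because start times there ignore progression. When progression itself triggers TCM, the PFS hazard ratio was 1.03 to 1.08. When only progression before 4 months triggers it, the ratio was far above 1.

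**Step 5. Candidate rules under no effect** (PFS medians of 3 to 6 months, start unrelated to progression and spread over 0 to 3 or 0 to 6 months):

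| Grouping rule | Spurious PFS hazard ratio |
|---|---|
| Section 3.7 as written | 0.61 to 0.84 |
| 12 weeks completed, started before progression | 0.44 to 0.68 |
| Same, and started by week 6 | 0.76 to 0.90 |
| Started by a 6-week landmark, completion not required, PFS counted from the landmark | 0.96 to 1.01 |

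The second rule worsens matters because it sends early progressors to the Western group, that is, it assigns exposure by the outcome.

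**The case against.** Four objections deserve an answer.

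*Sequential use is a deliberate choice, and a separate analysis plan could handle it.* The study may legitimately describe TCM in any order. But section 3.7 fixes the group definition itself. A later plan would have to override that definition, so this is more than a detail left to another document.

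*The affected group may be small.* This stands. Concurrent users are not miscredited, and a reader might wrongly infer that all integrated PFS, symptom and marker results are. Nor are the 19% to 47% of step 2 shares of the integrated group. For symptoms and markers, the article does not say which visits are compared between groups, and the data collection table is not visible. That part holds only if values recorded before TCM began enter the comparison.

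*TCM finished before enrollment.* A reader might infer that it counts, since section 3.9 specifies chemotherapy after enrollment ("If the times of chemotherapy after enrollment are ≤4 courses") and section 3.7 has no such wording. The text does not support this as a statement of fact. The ordering in section 3.7 is relative to Western treatment, not to enrollment; the groups are formed "according to whether they will receive TCM treatment or not", which points forward; and the eligibility table is not visible. The most that can be said is that the text shown does not exclude it.

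*This is a secondary-endpoint facet of the guaranteed-survival problem in OS.* It has the same cause, and the two should be corrected together. PFS still needs its own rule, because its event can precede the treatment.

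**Conclusion.** The point holds in this form: section 3.7 lets TCM begun after progression define the group for a PFS event that preceded it, and nothing in the article's analysis section corrects for that. It affects patients whose TCM fell outside the outcome interval. With start times unrelated to progression and assumed PFS medians of 3 to 6 months, a treatment with no effect would show a PFS hazard ratio of about 0.6 to 0.8 when TCM starts within 6 months, and as low as 0.54 if starts are spread over a year. These sizes rest on the assumptions listed under step 3, not on trial data. The direction is not fixed: it depends on why patients start TCM, which the rule leaves open. A claim that the PFS result must favour TCM would go too far, as would a claim that pre-enrollment TCM is counted.

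**What to change.** Change the analysis classification only; nothing here concerns patient care.

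- For PFS and the other time-dependent outcomes, define exposure as TCM started after enrollment and by a fixed landmark, for example the existing 6-week visit, whether or not 12 weeks are later completed. Count PFS from the landmark among patients still event-free.
- Alternatively, enter TCM as a time-varying covariate in the Cox model, with patients unexposed until their start date.
- Under either option, TCM first started after progression does not count as exposure for PFS.
- Do not use TCM started before progression as the sole grouping rule.
- Keep the 12-week, any-order grouping as a descriptive or sensitivity analysis, and report sequential users separately.

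The TCM dates needed are largely those already required to apply the 12-week rule, so the work is mainly wording and analysis. The cost is in numbers. With a 6-week landmark (42/30.44 = 1.38 months), exponential PFS implies that 1 − 0.5^(1.38/6) = 15% to 1 − 0.5^(1.38/3) = 27% of patients have an event before it and leave the PFS comparison. Late starters count as unexposed, which makes the exposed group smaller and dilutes the contrast somewhat; the time-varying model avoids both losses.

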### End point of observation

3.8

Patient death or the end of the study (October 31, 2021).

### Division of treatment period and follow-up period

3.9

If the times of chemotherapy after enrollment are ≤4 courses, the follow-up period will be entered after the end of chemotherapy; if the times of chemotherapy after enrollment are >4 courses, the follow-up period will be entered after the fourth chemotherapy.

## Study outcomes

4

### Primary outcomes

4.1

#### Overall survival (OS)

4.1.1

The primary outcome of this study is OS, which is from enrollment to patient death or the end of the study (October 31, 2021).

#### Secondary outcomes

4.1.2

##### Progression-free survival (PFS)

4.1.2.1

PFS, which is from enrollment to disease progression.

##### Tumor markers

4.1.2.2

Tumor markers, including CA199, CEA, and AFP, are closely related to the treatment of pancreatic cancer. They are used as one of the indicators to evaluate the effectiveness of treatment and are recorded at baseline and at each treatment visit and follow-up periods.

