##### TCM symptom assessment

4.1.2.3

TCM symptom grading scale for pancreatic cancer is based on the common symptoms of pancreatic cancer. It is used to observe pre- and post-treatment symptom improvement and includes 13 symptoms: poor appetite, low food intake, fatigue, jaundice, nausea and vomiting, abdominal distension, pain, fever, spontaneous sweating, loose stools, constipation, and insomnia. Each symptom has 4 grades, namely: none, mild, moderate, and severe, with corresponding scores of 0, 1, 2, and 3. The higher the score, the more severe the symptom.

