### Safety assessment

4.2

Routine blood tests and liver and kidney function tests are assessed at baseline, and functional damage is assessed at each follow-up visit. In addition, the investigator will ask subjects at each visit whether there are any adverse events (AEs), including physical discomfort or impairment. If there are any AEs, the investigator would provide appropriate treatment to the patient immediately and record it in the CRF at that time. Adverse effects are evaluated according to the National Cancer Institute (NCI) Common Terminology Criteria for Adverse Events.

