#### Data analysis

4.3.4

All statistical analyses will be performed using Statistical Packages of Social Sciences software (SPSS). A one-sided test (validity) will be used for all major efficacy indicators, and *P* values ≤.05 will be considered statistically significant. The measurement data will be expressed as the mean ± standard deviation, and the count data will be expressed using frequency and percentage. For quantitative indicators such as age, it is necessary to check whether the data meet the precondition of normality and homogeneity of variance. If the above conditions are met, a *t* test of measurement data of group design will be adopted. If only normality and not homogeneity of variance are satisfied, the calibration *t* test of measurement data in group design will be adopted. Otherwise, the Wilcoxon rank sum test will be used. For qualitative indicators such as sex, the general chi-square test will be performed according to the statistical analysis method corresponding to the data of the contingency table. If there is a frequency with a theoretical frequency <5, Fisher exact test will be used to directly calculate the exact probability. For survival data, the survival limit will be used to calculate the survival times of 25%, 50%, and 75% of each cohort. The log-rank test will be used to compare the survival rate, and the corresponding survival curve will be obtained.

For the analysis of influencing factors of efficacy, the univariate Cox regression model will be adopted in the first screen (*P* < .10), and the screened variables will then be fitted to the multivariate Cox regression model (*P* < .05).

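### Mean ± SD is fixed as the summary for all measurement data even where the test switches to rank sum, so a skewed tumor marker would be tested on ranks but reported by a mean that a few patients dominate.

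*Protocol article*

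**What the plan says.** Section 4.1.2.2 (Tumor markers) of the protocol article names three markers as secondary outcomes, CA199, CEA and AFP, and gives them an efficacy role: "They are used as one of the indicators to evaluate the effectiveness of treatment". They are "recorded at baseline and at each treatment visit and follow-up periods", so each patient has a baseline value.

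Section 4.3.4 (Data analysis) contains two rules that bear on them:

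- **Summary.** "The measurement data will be expressed as the mean ± standard deviation". No condition is attached, and no median, quartiles, geometric mean or log scale is named.
- **Test.** For quantitative indicators "it is necessary to check whether the data meet the precondition of normality and homogeneity of variance". If both hold, an ordinary t test is used. If only normality holds, a corrected t test is used. For the remaining case: "Otherwise, the Wilcoxon rank sum test will be used".

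The test thus adapts to the shape of the data and the summary does not.

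**The concern.** A summary and a test shown side by side should describe the same contrast. The rank sum test asks whether values in one group tend to be higher than in the other. The arithmetic mean of a strongly right-skewed variable is set largely by its upper tail. When section 4.3.4 sends a marker to the rank test because normality failed, it has already established that mean ± SD describes that marker badly, yet mean ± SD is still what the reader is given.

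Two consequences follow if the markers are strongly skewed. First, the reported means are imprecise and depend on a few patients. Second, the means can favour one group while the rank test favours the other, and a reader has no stated way to tell which one carries the result. The markers are offered as evidence of treatment effect, so this matters more here than for a descriptive variable such as age.

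**Working it through.** **Inputs**

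- Summary and test rules: section 4.3.4, as above.
- Group size: 148 patients in total at a 1:1 ratio (section 3.5), so 148 / 2 = 74 per group. The equal split is the planning assumption. Section 3.7 forms the groups only after the data are collected, so the real split may differ.
- Marker distribution: not given in the document. Log-normal values with log-SD s = 1.5, 2.0 and 2.5 are an **assumption**, shown as a range.

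The plan states no figure for the markers, so there is none to reproduce.

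**Step 1. How far the mean lies from the typical patient.** For log-normal data, mean / median = exp(s²/2).

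**Step 2. Precision of the mean.** Relative standard error of the mean = √(exp(s²) − 1) / √74.

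**Step 3. Precision on the log scale.** Standard error = s / √74. Its exponential is the factor within which the typical level is known (1 SE).

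| Assumed log-SD | Mean / median | Relative SE of mean | SE on log scale | Factor (1 SE) |
|---|---|---|---|---|
| 1.5 | exp(1.125) = 3.1 | 2.91 / 8.60 = 34% | 0.17 | 1.19 |
| 2.0 | exp(2.0) = 7.4 | 7.32 / 8.60 = 85% | 0.23 | 1.26 |
| 2.5 | exp(3.125) = 22.8 | 22.74 / 8.60 = 264% | 0.29 | 1.34 |

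The same patients thus give a poorly determined mean and a well determined typical level.

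**Step 4. How few patients drive the mean.** In simulated groups of 67 (half of the 134 in section 3.5, before dropout), the three largest values supply a median of 22%, 36% and 50% of the group's mean at log-SD 1.0, 1.5 and 2.0.

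**Step 5. Does the test share the problem?** In the same simulations a Shapiro-Wilk check (an assumed choice, since the document names none) sent every data set to the Wilcoxon test. With no true difference, that test rejected in 5.0%, 4.6% and 5.1% of trials at log-SD 1.0, 1.5 and 2.0, against a nominal two-sided 5%. It keeps its error rate, and each patient's influence is bounded by rank.

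**Step 6. Can the mean and the rank test disagree in direction?** Log-normal simulation, 74 per group:

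| Assumed log-SD | Two-fold difference, all trials | Two-fold difference, trials with two-sided rank P < .05 | 1.5-fold difference, all trials |
|---|---|---|---|
| 1.5 | about 4% | about 2% | about 15% |
| 2.0 | about 15% | about 8 to 9% | about 26% |
| 2.5 | about 24% | about 14 to 15% | about 32% |

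Entries are the share of trials in which the difference in means has the opposite sign to the rank comparison. At the upper end, roughly one significant rank result in seven would stand beside means that favour the other group.

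**The case against.** The strongest reply is that the plan already handles skewness where it counts. The normality check and rank sum fallback protect the comparison, and step 5 bears this out. That stands: a reader might infer that a few extreme patients decide the marker result, and the document does not support it. Only the descriptive mean is exposed.

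A second reply is that the spread of the markers is not in the document. That also stands. The sizes above are conditional on the assumed log-SD. The mismatch between summary and test does not depend on it: it arises for any variable that fails the check.

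A third concerns who is measured. A reader might infer that jaundiced patients, or patients whose markers are never elevated, distort the result. The document does not support treating this as an error. Section 4.1.2.2 does not say that every patient enters the marker analysis. The eligibility table is not shown, so an exclusion for jaundice can be neither confirmed nor ruled out. Jaundice appears only as one item of a symptom scale ("poor appetite, low food intake, fatigue, jaundice, nausea and vomiting"), which does not show that obstructed patients are enrolled. The safety section says "Routine blood tests and liver and kidney function tests are assessed at baseline" but never names bilirubin. How CA199 behaves under biliary obstruction is outside knowledge, and no marker-response criterion is defined that such patients could fail or falsely meet. A never-elevated patient is also not an extreme value and would at most dilute a contrast.

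Finally, the detailed handling of a secondary marker commonly belongs in the analysis plan. That is true of subsets and sensitivity analyses. It does not cover the summary rule, which this document states and fixes without condition.

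**Conclusion.** The point holds in a narrow form. Section 4.3.4 prescribes mean ± SD for all measurement data, including data its own check has found non-normal and moved to a rank test. For the three efficacy markers, if they are strongly right-skewed, the reported means would be dominated by a few patients and could contradict the direction of the test.

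The size rests on log-normal values with log-SD 1.5 to 2.5 and 74 per group, none of which the document establishes for the markers. Under these assumptions the mean is 3 to 23 times the median, and its standard error is 34% to 264% of its value. The validity of the between-group test is not in question, and the primary outcome is untouched. This is a low-severity improvement that would be good to have, not an error that threatens the study's conclusions.

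**What to change.** **In section 4.3.4**, make the summary follow the test: mean ± SD where the normality check is met, and median with quartiles, or geometric mean, where it is not.

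**For CA199, CEA and AFP**, state that groups are compared on the log ratio of the on-study value to the patient's own baseline, log(value / baseline), with the result reported as a geometric mean ratio or a median ratio. If the markers are close to log-normal, this ratio is close to normal, and the summary and test then agree. It also takes account of each patient's starting level, which is useful where groups are formed by treatment received. It does not remove confounding between the groups.

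**Optional, for the analysis plan:** a sensitivity analysis in patients with elevated baseline CA199, and a stated approach to samples taken during jaundice. Excluding follow-up samples by jaundice conditions on a post-baseline state that treatment may affect, so it should not be the main analysis.

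**Cost:** a sentence or two of analysis wording. Baseline markers are already recorded, no new data are needed, and the sample size and primary analysis do not change.
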